### Aim 2: Effectiveness of OPCs in the surrounding community

Our study will also assess whether and how the opening of OPCs impacts neighborhood conditions. Specifically, we will use causal inference techniques to evaluate whether census block groups surrounding the OPCs in NYC and RI experience a greater change in overdose, public disorder, and economic conditions compared to what their changes would have been if they hadn't opened the OPCs.

#### Defining the neighborhood around an OPC

We will utilize four geospatial methods to define the treatment area near an OPC. The first will be based on prior work. [17, 53] We anticipate that the majority of people who use an OPC will reside within a radial 500 m (~ 20 min walking radius) of the facility, and thus the community-level effects of an OPC (if present) will be largest in this area. [39, 54–56] To approximate the neighborhood surrounding an OPC, we will create a 500-m Euclidean distance buffer and will identify the census block groups within this buffer. All census block groups that contain this buffer will define the ‘intervention’ neighborhood (Fig. 2). [57] The second will incorporate machine learning with geostatistical methods to determine an optimal buffer radius distance and will include census block groups that are within this distance as the treatment area. [58] The third utilizes data collected from the surveys. We will construct a participant-informed radius using self-reported data on the zip code that a participant spends most of their time, the usual amount of travel time to the OPC, and method of transportation to the OPC. The last method will incorporate optimal street networks using kernel density estimation with a barrier, resulting in an asymmetrical buffer that excludes features such as expressways and other regions where study outcomes cannot occur.

**Fig. 2 Fig2:**
[figure not shown]
Locations of existing and proposed OPCs, with a 500-m street network buffer (blue) and census block groups intersecting with this buffer (dashed line)

#### Neighborhood-level outcomes of interest

Since OPCs provide an environment where medical attention can be readily provided in the event of a drug overdose, we hypothesize that the opening of an OPC will be associated with significant decreases in the rate of drug overdose in neighborhoods where they are located. Using vital statistics records from the NYC Office of Chief Medical Examiner and the RI Office of State Medical Examiners, [59, 60] we will map drug overdose deaths based on the injury location on the death certificate. [61] We will define drug overdose deaths using underlying cause of death codes (X40-X44). [62] To measure non-fatal overdoses, we will use multiple data sources (Table 2), including Medicaid and EMS runs for suspected overdoses, and map these incidents based on their geographic coordinates (i.e., location of injury). [63]

Based on evaluations conducted in other settings, [11, 64–67] we also hypothesize that the opening of an OPC will be associated with improvements in measures of public safety, by bringing drug use indoors. Using publicly available arrest records from the NYC Police Department and the Providence Police Department, [68, 69] we will map the locations of drug-related offenses (e.g., possession of a controlled substance, criminal sale of a controlled substance) and other interpersonal crimes (e.g., assault, theft, larceny) as in prior work, [64] based on the location associated with each arrest.

Should the opening of an OPC be associated with improvements in public safety, we also hypothesize that the opening of an OPC will be associated with improvements in property values. Using publicly available data from the NYC Department of Finance and Providence Department of Finance, [70, 71] we will map historical property valuations and real estate sales to identify changes in assessed value and actual sale prices.

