## Materials and methods

### Theoretical framework

Our work is guided by the intersectional risk environment framework, [33] which draws attention to how structural (e.g., economic conditions), social (e.g., racism, stigma), and physical (e.g., availability of treatment programs) environments produce inequitable outcomes based on intersecting social identities (e.g., gender, race). By modifying the physical environment in which drugs are consumed and potentially attracting a new population who was not previously engaged in services, we hypothesize that OPC use will result in numerous health and social benefits to people who access them. Our framework guides survey development, data collection, and analytic strategies. The intersectional risk environmental framework also recognizes that people who use drugs (PWUD) are not only affected by their risk environments, but also interact with and influence it. Hence, we hypothesize that communities in which OPCs are located will experience public health, public safety, and economic benefits by increasing health, treatment, and social services engagement among PWUD. Finally, the framework acknowledges that PWUD differentially experience socio-economic marginalization and social discrimination, which produces inequitable patterns of service engagement based on social positions. Thus, in our qualitative work, we adopt ethno-epidemiological methods [34] to understand how operational contexts, program models, and operating procedures influence program effectiveness for sub-populations of PWUD (e.g., women, racialized PWUD), including in relation to key outcomes. A summary of our aims, approach, and the timeline for data collection activities is shown in Fig. 1. Methods are described below by study aim.

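### Aim 2 counts overdoses where they happen, a sound choice for a neighborhood effect, but nothing in the model or stated assumptions separates drug use that moves between areas from deaths prevented or caused

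*Protocol article*

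**What the plan says.** Under *Neighborhood-level outcomes of interest*, the article fixes the location rule for deaths: "we will map drug overdose deaths based on the injury location on the death certificate". For non-fatal overdoses it will "map these incidents based on their geographic coordinates (i.e., location of injury"), so both outcomes follow the place of the event. No count by residence is mentioned.

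Under *Defining the neighborhood around an OPC*, it announces: "We will utilize four geospatial methods to define the treatment area near an OPC". They are:

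- **First:** a 500 m buffer, justified by the expectation that "the majority of people who use an OPC will reside within a radial 500 m" of the facility.
- **Second:** "The second will incorporate machine learning with geostatistical methods to determine an optimal buffer radius distance".
- **Third:** a radius built from "self-reported data on the zip code that a participant spends most of their time, the usual amount of travel time to the OPC", plus mode of transport.
- **Fourth:** a street-network density that leaves out places where outcomes cannot arise.

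Under Aim 2, *Analyses*, the estimand is the ATT for neighborhoods that opened an OPC. A linear regression supplies the counterfactual count. The covariates named as examples are demographics, past overdose rates and harm reduction services. The stated difficulties are unmeasured confounding (with an E-value analysis), time-varying confounding, clustering and model form. The study aims in the Introduction name the comparators as block groups unexposed to OPCs.

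**The concern.** By the article's own account the intervention alters the setting in which drugs are consumed (*Theoretical framework*), and it is expected to bring use indoors (*Neighborhood-level outcomes of interest*). The third area definition collects travel time and transport, so some clients are expected to travel in. The amount of drug use inside a treated area may therefore respond to the opening, and a count by injury location combines that response with any change in the risk of death.

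Two consequences follow.

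1. **Interpretation.** A fall in the area could be use that moved elsewhere, and a rise could be use that moved in, with no change in total deaths.
2. **Identification.** If use moves between treated and comparison block groups, the comparators are no longer unaffected, and the estimated counterfactual is wrong even for a purely place-based effect.

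The Discussion says the results are meant to inform legal and policy debate, where deaths moved and deaths prevented mean different things.

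**Working it through.** The article gives no event count, effect size or power for Aim 2, so there is no figure to reproduce. The check has two parts.

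**Part 1. Reading the text for any safeguard.**

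- Outcome: place of injury, for fatal and non-fatal events.
- Covariates named: none reflects where drugs are used after opening.
- Assumptions and limitations: neither Aim 2, *Analyses* nor the Discussion mentions displacement, spillover or interference.
- Sensitivity analysis: the E-value addresses unmeasured confounding, not movement between areas.
- Area and outcome: the first definition argues from residence, while the outcome is counted by place of event. A majority living within 500 m still allows nearly half to live outside, and a death averted at such a client's home is not counted in the treated area.

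**Part 2. How large the mixing could be.** Let *e* be the true proportional reduction in deaths per unit of drug use in the area, and *m* the net change in drug use in the area caused by movement across its boundary. Use that moves from nearby streets into the supervised site belongs to *e*, not *m*. The values of *m* are assumed. The 35% is the Vancouver figure cited in the Introduction and serves only as an example. The plan's ATT is a difference in deaths; a ratio is used here because no baseline count is given.

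Apparent rate ratio = (1 − *e*) × (1 + *m*)

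| *m* (assumed) | *e* = 0 | *e* = 0.35 |
|---|---|---|
| −20% | 1 × 0.80 = 0.80 | 0.65 × 0.80 = 0.52 |
| −10% | 1 × 0.90 = 0.90 | 0.65 × 0.90 = 0.585 |
| 0 | 1.00 | 0.65 |
| +10% | 1 × 1.10 = 1.10 | 0.65 × 1.10 = 0.715 |
| +20% | 1 × 1.20 = 1.20 | 0.65 × 1.20 = 0.78 |

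A true 35% reduction would thus read as anything from 22% (1 − 0.78) to 48% (1 − 0.52).

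Now suppose the OPC changes no one's risk, 10% of treated-area use moves into the comparison block groups, and total deaths stay the same. With *w* the treated areas' share of all deaths in treated and comparison areas (assumed):

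Apparent ratio = (1 − 0.10) / (1 + 0.10 × *w*/(1 − *w*))

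- *w* = 2%: 0.90 / 1.002 = 0.898
- *w* = 10%: 0.90 / 1.011 = 0.890
- *w* = 30%: 0.90 / 1.043 = 0.863

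Most of the distortion is the 0.90 in the treated area itself. Contamination of the comparators adds 0.002, 0.010 and 0.037 respectively, so it matters mainly when the treated areas hold a large share of the deaths.

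**What a ring would show.** Assume 10 deaths a year in the treated area and 10% of use moving just outside it. The treated count falls by 1, the ring count rises by 1, and the sum is unchanged. A true local reduction would lower the sum.

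**The case against.** The strongest reply is that the outcome matches the estimand. Aim 2 asks about places, and deaths occurring in a place are what a neighborhood ATT counts. If an opening draws unsupervised use into the area, the resulting deaths are part of the neighborhood effect. This stands: injury location is a defensible primary outcome. It does not answer the contamination of comparators, or a reading of the result as net deaths prevented.

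Other points also have force:

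- A reader might infer that the treated area was chosen because clients live there. That describes only the first of four definitions; the third uses where participants spend their time and the fourth refers to where outcomes can arise.
- A reader might take the *Theoretical framework* remark about "potentially attracting a new population who was not previously engaged in services" as a forecast of geographic inflow. It concerns engagement with services. The New York sites are co-located in existing syringe service programs, so some clients may already have been coming there.
- Aim 1 links participants to medical examiner records and models fatal overdose against OPC use, with no stated restriction to the neighborhood. This covers part of the person-level question, but only for the recruited cohort (target 1000), not the community.
- Varying the boundary over four definitions gives some information on nearby displacement, though it is not set up as a test of it.
- This is a condensed article, and a ring analysis may sit in a document not shown. However, the article gives a detailed account of what makes the Aim 2 question hard, and movement of drug use is not in it.

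**Conclusion.** The point holds in a limited form. The text places overdoses only by where they occur, and neither the model nor the stated assumptions distinguish a shift of use between areas from a change in deaths. The residence argument for the first area definition does not match that outcome.

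The documents do not support a stronger claim that the outcome is wrong, or that the result will be biased in a known direction or by a known amount. The illustrated ranges (0.80 to 1.20 with no true effect; 0.52 to 0.78 around a true 0.65) rest wholly on assumed shifts of 10% to 20% and on moved use carrying the same risk of death wherever it takes place. What can be said is that modest shifts would be large enough to alter the message, and that the plan as described has no designated way to detect them.

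**What to change.** 1. Keep injury location as the primary outcome.
2. Prespecify the same ATT analysis for a ring of block groups just outside each treated area, as a displacement check. Fix the ring's width before outcome data are seen, and leave it out of the comparison set. Report treated-area and ring estimates together, with their sum in deaths.
3. Where the medical examiner records hold the decedent's residence (an assumption; the article does not say so), co-report a residence-based count with the number missing or unhoused. Residence alone cannot settle the matter, because it misses non-residents who use drugs near the site.
4. Add to Aim 2, *Analyses* an explicit assumption that an opening does not affect overdoses in comparison block groups.
5. Describe the primary result as a change in deaths occurring in the area, and speak of net deaths prevented only if the ring result supports that.

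The cost is a repeat of a model already planned, possibly one further geocoded field, and slightly fewer comparison block groups. With at most three OPCs, the added estimates will probably be imprecise and should be presented as secondary. A ring detects only local movement; shifts to or from distant areas remain covered by assumption alone.

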## Introduction

More than 100,000 people died of an overdose in 2022 in the United States. The age-adjusted rate of overdose deaths almost quadrupled from 2002 to 2022, making overdoses one of the leading causes of injury death in adults. [1] Fentanyl and other illegally manufactured synthetic opioids drive overdoses and have contributed to historically high levels of death from overdose since 2014, starting in the East Coast and shifting to the West Coast in more recent years. This crisis has coincided with rapidly rising rates of hepatitis C virus infection, HIV outbreaks, and other sequelae of unsterile drug use. [2–4] The economic cost of the crisis exceeds $1 trillion annually. [5]

Persistently high levels of overdose in the United States have led to a call for new solutions. Overdose prevention centers (OPCs) have been proposed as a strategy to reduce drug-related harms in the context of a volatile illegal market dominated by highly lethal products. OPCs (also known as supervised consumption sites, safe injection facilities, drug consumption rooms, or harm reduction centers) are community-based facilities at which clients consume pre-obtained controlled substances under the supervision of personnel trained to intervene in the event of an overdose. [6] In most countries, OPCs resemble community health clinics, with booths that permit supervision by trained personnel. OPC staff also provide education about safer drug consumption practices, access to sterile supplies, referrals to other treatment, health, and recovery services. While OPCs have long been in operation in other countries, no publicly recognized OPCs existed in the United States before 2021. In July 2021, Rhode Island (RI) became the first state to authorize OPCs through legislation; the first OPC service will open in Fall 2024. [7] In November 2021, the first two publicly recognized OPCs in the US opened in New York City (NYC). [8–10]

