#### Outcomes measured through administrative health records

To provide a comprehensive assessment of change in health conditions associated with OPC use, we complement self-reports with administrative health records. Participant identifiers will link participants to their administrative health records. Table 2 presents the sources and types of information we plan to collect, leveraging our partnerships with the NYC Department of Health and Mental Hygiene (DOHMH), NYS Office of Addiction Services and Supports (OASAS), the RI Department of Behavioral Health, Developmental Disabilities, and Hospitals (BHDDH), and the Rhode Island Department of Health (RIDOH). We link participants to their health records 18 months prior to their first survey date and for up to three years post-enrollment, to track pre- and post-OPC changes in their health using probabilistic matching with the last four digits of each participants’ social security number, first and last name, date of birth, and sex. [42] We use a minimum, common set of data sources, including Medical Examiner, Medicaid, and data from licensed substance use disorder treatment facilities (through OASAS and BHDDH), ensuring a high degree of comparability across jurisdictions. In Rhode Island, we can also link participants to prescription drug monitoring program data, as we have done in prior work. [43]

**Table 2 Tab2:** Administrative health record data sources linked with study participants

Domain	Items	NYC data^1^	Rhode Island data^2^
Fatal overdose	All drug overdose, stimulant, and opioid	Office of Chief Medical Examiner	Office of Chief Medical Examiner
Non-fatal overdose	All drug overdose, stimulant, and opioid	NYC Regional Health Information Exchange (RHIO), Statewide Planning and Research Cooperative System (SPARCS),^3^ Medicaid	Emergency medical services data, Medicaid^4^
Drug-related health conditions	Hepatitis C, HIV, skin and soft-tissue infections, infective endocarditis	NYC RHIO, SPARCS, and Medicaid	Medicaid^4^
Emergency department visits	Overall ED use, drug-related emergency department (ED) visits	NYC RHIO, SPARCS, and Medicaid	Medicaid^4^
Substance use disorder treatment	Initiation in a licensed treatment program, including medications for OUD	OASAS and Medicaid	Prescription drug monitoring program, BHDDH, and Medicaid

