Second, we will test the hypothesis that OPC use (any past month use, intensity of use, fraction of drug use) is associated with lower hazard and recurrence of non-fatal overdoses, by fitting MS-MSCM. We will account for the same types of potential confounders as considered for non-recurrent outcomes. We will fit the same type of MS-MSCM models for other recurrent and interrelated outcomes, including skin and soft-tissue infections, infective endocarditis, and emergency department use.

Following the intersectional risk environment framework, [33] we will conduct intersectional analyses to determine whether primary outcomes of interest (e.g., uptake of substance use treatment) vary by intersecting social positions and identities (e.g., race, gender). We will employ intersectional methods such as stratification and inclusion of interaction terms, as appropriate. [51] More novel approaches such as multilevel analysis of individual heterogeneity and discriminatory accuracy will also be explored. [52] Finally, we will conduct exploratory stratified analyses to determine whether observed effects vary by jurisdiction (RI vs. NYC).

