#### Determine start-up and ongoing costs of OPCs

We will use established micro-costing methods to estimate the operational costs of OPC study sites in RI and NYC. [90, 91] One-time start-up costs (e.g., staff training, equipment purchases), ongoing variable costs (e.g., staff labor time for each service delivered), ongoing time-dependent costs (e.g., regular staff meetings, record-keeping), and overhead costs will be calculated from the budgetary perspective of the study sites. Cost calculations will use resource costing methods which are computed by multiplying the price weight for each resource unit by the respective units of service and then summing the values across all services. [92, 93] Labor costs will be valued using local wage rates for comparable OPC staff positions from the Bureau of Labor Statistics as well as national wage rates for sensitivity analysis.

We will use site records on services provided to OPC clients, estimates of the time required to provide services obtained through staff interviews at each site, and site financial records to conduct cost analyses. We will adapt the Drug Abuse Treatment Cost Analysis Program (DATCAP) instrument to conduct data collection. [94] Results will be reported as annual costs for each of the sites and as a total average for each location (RI and NYC). For each total cost result reported, each cost component will be reported (i.e., start-up, ongoing (i.e., variable and time-dependent costs), and overhead costs). We will also report total costs per client served and per overdose reversed.

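### In Aim 2, non-fatal overdose is measured only from emergency or billed contacts, which on-site OPC care can replace, so a change in the count is not a change in overdose occurrence

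*Protocol article*

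**What the plan says.** The Introduction describes an OPC as a place where "clients consume pre-obtained controlled substances under the supervision of personnel trained to intervene in the event of an overdose". Under Aim 2, Neighborhood-level outcomes of interest, the hypothesis is that "the opening of an OPC will be associated with significant decreases in the rate of drug overdose in neighborhoods where they are located". The reason given is: "Since OPCs provide an environment where medical attention can be readily provided in the event of a drug overdose".

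Non-fatal overdose in Aim 2 is taken from multiple sources with a pointer to Table 2, "including Medicaid and EMS runs for suspected overdoses, and map these incidents based on their geographic coordinates". Table 2 lists a regional health information exchange (RHIO), SPARCS and Medicaid for NYC, and EMS data and Medicaid for Rhode Island.

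In Aim 1 (Analyses), outcomes come from both administrative records and surveys. The hypothesis there is that OPC use "is associated with lower hazard and recurrence of non-fatal overdoses". Overdoses in the last 30 days are asked about in the surveys and at each monthly check-in.

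On-site reversals appear once, as a cost denominator in Aim 4: "We will also report total costs per client served and per overdose reversed".

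**The concern.** The stated mechanism acts once an overdose has begun. It explains why fewer people should die, but not why fewer should overdose. It does explain why fewer overdoses should reach an ambulance, an emergency department or a claim. An overdose managed by OPC staff need not leave any of these traces, whereas the same event on the street may. The measure is therefore sensitive to where an overdose is treated as well as to whether it happens.

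At stake is the conclusion. If the plan is followed as written, a drop in recorded events could be reported as fewer overdoses when only the place of treatment has changed. Less emergency use would be a real benefit, but it is a different claim. The assumptions discussed under Aim 2, Analyses (confounding, positivity, clustering, model form) and the limitations in the Discussion do not mention capture that depends on exposure. E-values address unmeasured confounding, and the Aim 1 weights address confounding and censoring. None of these corrects an outcome that is recorded differently by exposure.

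**Working it through.** The article gives no expected count, effect size or power for non-fatal overdose, so there is no figure of its own to reproduce. The check asks what the record-based count would show if opening an OPC changed no overdoses at all.

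**Inputs.** All are assumptions, as the article states none of them.
- f: the share of all overdoses in the area, including those of non-clients, that occur inside the OPC after opening.
- c: the probability that an off-site overdose enters a record.
- s: the same probability for an on-site overdose.
- k = s/c: relative capture.

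**Formula.** Take N overdoses before opening, all off site, and N after, with c unchanged.
- Recorded before: cN.
- Recorded after: c(1 - f)N + s·f·N.
- Ratio: (1 - f) + f·s/c = 1 - f(1 - k).

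**Results with no true effect.**

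| f | k = 0 | k = 0.25 | k = 0.5 | k = 1 |
|---|---|---|---|---|
| 0.10 | 0.90 | 0.925 | 0.95 | 1.00 |
| 0.25 | 0.75 | 0.8125 | 0.875 | 1.00 |

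The artefact vanishes only if on-site and off-site overdoses are equally likely to be recorded (k = 1), or if f is zero.

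**Direction.** Suppose people from outside the block groups add on-site overdoses equal to m times those that moved on site from the area. The ratio becomes 1 - f + f·k·(1 + m). With f = 0.25 and m = 1:
- k = 0: 0.75 + 0 = 0.75
- k = 0.5: 0.75 + 0.25 × 0.5 × 2 = 1.00
- k = 1: 0.75 + 0.25 × 1 × 2 = 1.25

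The mapped count can therefore fall, stay level or rise with no change in overdose occurrence.

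**Effect of adding on-site reversals.** If every on-site overdose is counted once, s = 1 and k = 1/c. With c = 1 and m = 0 the ratio is 1.00. With c = 0.5 (assumed) and f = 0.25 it is 1 - 0.25 × (1 - 2) = 1.25. Adding reversals can thus overcorrect when off-site capture is incomplete, which is why both counts are needed.

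**Aim 1.** The same algebra applies to the linked records, with f as a participant's own on-site share. If overdoses follow the place of use, f rises with the planned exposure measure, the fraction of drug use at an OPC, so the artefact could resemble a dose-response. Self-report is not tied to an emergency contact and offsets this in part.

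**The case against.** The strongest case on the other side has several parts.

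- **Aim 1 does not rest on records alone.** Self-reported overdose is collected at surveys and check-ins, and the Discussion presents the combination of sources as a strength. This stands. A reader might infer that the Aim 1 non-fatal result is unusable, but the article does not support that. The problem is confined to the record-based part.
- **The survey instrument is not shown.** Table 1 is a summary, and the baseline instrument is in an appendix. It cannot be said that participants are never asked where an overdose happened.
- **The size is easily overstated.** A reader might take f near 0.5 from the cut at more than 50% of drug use in Aim 1. That cut concerns individual clients and compares them with lower use, not with none. It says nothing about a neighbourhood count that includes non-clients. Nor is s alone enough: what matters is capture relative to off-site events.
- **The direction is not fixed.** A reader might conclude that records must fall. The outside-client calculation shows otherwise.
- **NYC EMS data may well be available.** Table 2 describes linkage of study participants, and the Aim 2 text names EMS runs without limiting them to Rhode Island. The loose cross-reference does not show that NYC lacks EMS data.
- **Deaths are the worked example.** The Aim 2 causal question and estimator are written for overdose deaths, which come from medical examiner records and are not subject to this capture problem.

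Rules for combining sources can be left to a fuller plan. The hypothesis and the sources named for it in Aim 2 are stated in this article, however, and they do not match.

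**Conclusion.** The concern holds for Aim 2 non-fatal overdose. Every named source requires an emergency or billed contact that on-site intervention can replace, so the count cannot be read as the rate of overdose. With no true effect and no outside clients, the apparent reduction would be 5% to 10% at f = 0.10 and 12.5% to 25% at f = 0.25, for k between 0 and 0.5. These figures rest on assumed f and k and on constant off-site capture. With outside clients who still trigger EMS, the artefact could disappear or reverse. An uncertain direction does not rescue the interpretation. The record-based part of Aim 1 is affected to a lesser degree. Fatal overdose is not affected by this problem, and fewer emergency contacts is a valid finding under its own name.

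**What to change.** 1. Name the record-based outcome *overdose with EMS or hospital contact* in both aims, and limit the conclusion to that.
2. In Aim 2, report it with and without the OPC sites' on-site reversal counts, which Aim 4 already needs, after removing reversals that also generated a record. Read the two as a sensitivity range, not as a biased and a corrected figure: incomplete off-site capture or clients from outside the area can push the second count too high.
3. In Aim 1, report self-reported and record-based overdose separately. If the instrument does not already ask it, add one check-in item on how many of the reported overdoses happened inside an OPC.
4. Clarify the Aim 2 reference to Table 2 by stating which source supplies mapped EMS incidents in NYC.

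The cost is wording, reuse of site records with a de-duplication step, and at most one survey item. The downside is a possibly less favourable effect on non-fatal overdose.
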